### Study design

This study is an ongoing multicenter, population-based prospective cohort study conducted in three TB designated hospitals in Eastern and Western China. The study aims to include 300–400 bacteriologically confirmed pulmonary TB patients. Baseline information, including demographics, socioeconomic status, laboratory tests, and disease profiles, as well as sputum and stool samples will be collected from the enrolled patients immediately after TB diagnosis. The patient cohort will be built and followed up during the first-line anti-TB treatment at Day-14, Month-2, Month-5, last day of treatment, and the sixth month after treatment. Information regarding adverse effects, disease progress, and laboratory results will be collected at each visit. Stool samples will be sent to the laboratory for 16S ribosomal ribonucleic acid (rRNA) gene sequencing to identify the alterations in gut microbiota. A comparison of gut microbiota will be performed between newly diagnosed TB patients and healthy controls to reflect the difference in baseline features. After treatment completion, a nested case-control study will be performed between patients with treatment success or failure and patients with or without adverse effects to screen the potential biomarkers from the gut microbiota indicative of therapeutic effect.

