#### Microbiome analysis

The raw 16S rRNA gene data will be processed to generate amplicon sequence variants (ASVs) using DADA2 program [25]. Taxonomies will be assigned using Silva [26] as the reference database. Alpha diversity (such as Observed ASVs, Chao1, Shannon, Simpson, etc.) and beta diversity measures will be analyzed using QIIME2 [27] and the Wilcoxon and Kruskal–Wallis tests will be used for statistical testing of two and multi-group comparisons, respectively. Principal coordinate analysis will be used to interrogate the robustness of group-wise clustering, and Adonis test will be used to estimate statistical significance of group-wise beta diversity [27]. Generalized linear model (GLM) will be performed to evaluate the influence factors that may affect the gut microbiota of patients, such as gender, body mass index, TB severity, age, morbidities and so on [28]. Then using GLM to estimate the dynamic changes of microbiota composition with the control of selected confounders [29]. Differential abundance analysis of ASVs will be carried out using STAMP [30] and *p*-values will be adjusted for multiple testing (FDR-adjusted Wald Test). Correlations between clinical parameters and bacterial genera will be calculated using canonical correspondence analysis or redundancy analysis [31]. Random forests approach will be performed to find the most important species as marker taxa correlating with unfavorable treatment outcomes. The data will be analyzed using the QIIME2 pipeline and R [32]. A *p*-value or q-value ≤0.05 will be considered as statistically significant.

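### Confounder control is stated only for the model of microbiota change over time; none is stated for the outcome comparisons and marker search, so taxa that track baseline severity can surface as outcome markers

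*Protocol article*

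**What the plan says.** All of the following is in the protocol article.

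- **Outcome comparison.** The abstract plans to compare microbiota diversity and components between patients with and without an unfavorable outcome. The Study design section makes this a nested case-control study (success versus failure; adverse effects versus none), "to screen the potential biomarkers from the gut microbiota indicative of therapeutic effect". No matching rule is given. Secondary objectives 3 and 4 depend on it.
- **Methods for group comparisons** (Microbiome analysis). For diversity, "the Wilcoxon and Kruskal–Wallis tests will be used for statistical testing of two and multi-group comparisons, respectively". For community structure, "Adonis test will be used to estimate statistical significance of group-wise beta diversity". For single features, "Differential abundance analysis of ASVs will be carried out using STAMP", with p-values adjusted for false discovery rate. For markers, "Random forests approach will be performed to find the most important species as marker taxa correlating with unfavorable treatment outcomes".
- **Covariates.** One GLM has this aim: "evaluate the influence factors that may affect the gut microbiota of patients, such as gender, body mass index, TB severity, age, morbidities and so on". The only stated control of confounding follows it: "Then using GLM to estimate the dynamic changes of microbiota composition with the control of selected confounders". In both models the microbiota is the response, and treatment outcome does not appear.
- **Data.** The Study procedures section has TB severity recorded after consent. Table 2 lists age, sex, comorbidities and a physical examination at Day-0. BMI is not a named item in Table 2.

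**The concern.** The plan recognises that severity, age and comorbidity may shape the microbiota, and it collects data on them before treatment. It then states adjustment for the longitudinal question and none for the outcome question. Confounding of the outcome question is at least as plausible: any of these factors that also raises the risk of failure or of adverse effects will make the outcome groups differ in every taxon it influences, even if no taxon bears on outcome.

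At stake are objective 3 (association of dysbiosis with outcome), objective 4 (marker taxa), and the Discussion's expectation that the findings could guide personalised treatment. Even for a purely predictive marker, a ranking of species alone does not show whether stool sequencing adds anything to what is known clinically at Day-0.

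**Working it through.** **1. Where adjustment is stated**

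| Analysis | Serves | Adjustment stated |
|---|---|---|
| GLM of influence factors | Determinants of the microbiota | The factors are the predictors |
| GLM of dynamic change | Change over time | Yes, selected confounders |
| Wilcoxon / Kruskal–Wallis | Group comparisons | None; these tests take no covariates |
| Adonis | Group-wise beta diversity | None |
| STAMP | Differential abundance | FDR only, which addresses multiplicity |
| Random forest | Unfavorable outcomes | None |

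Only the random forest is tied by name to unfavorable outcomes. The other group methods are listed generically, but no different method is given for the outcome groups.

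**2. The plan's own event count.** From the Sample size section: 3 sites × 50 per year × 2 years = 300 patients, and 10% of 300 = 30 unfavorable outcomes. This reproduces and gives group sizes of 30 and 270.

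**3. How large the effect could be.** From the documents: 300 patients, 10% failure, 5% significance level. Assumed: a binary severity factor present in 30% of patients, an odds ratio (OR) for failure, and a shift d (in SD) that the factor causes in a diversity index or taxon which itself has no link to failure.

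- Let p0 be the failure risk without the factor and p1 the risk with it. Solve 0.3·p1 + 0.7·p0 = 0.10, where p1/(1−p1) = OR·p0/(1−p0).
- Prevalence of the factor is 0.3·p1/0.10 among failures and 0.3·(1−p1)/0.90 among successes.
- Spurious group difference: Δ = d × (difference in prevalence).
- With z = Δ/√(1/n1 + 1/n2), the two-sided rejection rate is Φ(z − 1.96) + Φ(−z − 1.96).

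Worked case, OR 3 and d = 0.5: p0 = 0.067 and p1 = 0.177. The factor is present in 53.1% of failures and 27.4% of successes, a difference of 0.257. Δ = 0.5 × 0.257 = 0.129. For 30 versus 270, √(1/30 + 1/270) = 0.192, so z = 0.67 and the rejection rate is 10.2%.

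| OR | Factor in failures / successes | d (SD) | Δ (SD) | 30 vs 270 | 30 vs 30 |
|---|---|---|---|---|---|
| 1 | 30.0% / 30.0% | any | 0 | 5.0% | 5.0% |
| 2 | 44.3% / 28.4% | 0.5 | 0.079 | 7.0% | 6.1% |
| 2 | 44.3% / 28.4% | 0.8 | 0.127 | 10.1% | 7.8% |
| 3 | 53.1% / 27.4% | 0.5 | 0.129 | 10.2% | 7.9% |
| 3 | 53.1% / 27.4% | 0.8 | 0.206 | 18.8% | 12.5% |
| 4 | 59.3% / 26.7% | 0.5 | 0.163 | 13.5% | 9.7% |
| 4 | 59.3% / 26.7% | 0.8 | 0.261 | 27.3% | 17.3% |

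**4. Simulation check.** With n = 300, 10% failure, 30% factor prevalence and 2000 runs per scenario, the unadjusted Wilcoxon test rejected in 4.8% (OR 1), 7.0% (OR 2) and 9.5% (OR 3) of runs at d = 0.5. At d = 1 it rejected in 10.3% (OR 2), 20.9% (OR 3) and 33.5% (OR 4). A linear model with the severity factor added rejected in 4.3% to 5.5% across all six scenarios.

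FDR adjustment does not remove this excess, because it presumes valid null p-values. The calculation covers one two-group test. It does not quantify the random forest, which has no 5% error rate, although the same mechanism can raise a severity-tracking taxon in its ranking.

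**The case against.** **Condensed article.** This is a journal article, and a feature list for the forest, Adonis terms or a matching rule may sit in a fuller document. A reader might infer that the clinical variables are deliberately kept out of the forest. The text does not say so; it neither includes nor excludes them. The Wald test mentioned with STAMP could also come from a regression model. These points stand and limit the finding to what is stated. They do not dispose of it: the section says where confounders are controlled and names only the model of change over time, and the test it assigns to two-group comparisons cannot take covariates.

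**Other safeguards.** Eligibility is limited to ages 18–65 and excludes gastrointestinal disease, severe liver or renal disease, recent antibiotics and MDR-TB. The GLM of influence factors, and the canonical correspondence or redundancy analysis of clinical parameters, would show which taxa follow severity. These narrow the problem and make it visible, but they do not adjust the outcome comparison.

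**Screening aim.** The text speaks of potential markers that correlate with outcome, and such a marker need not be independent of severity. That is fair for a first screen. It does not answer objective 3, which concerns association, nor the stated hope of guiding treatment.

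**Certainty.** A reader might infer that markers of sicker patients will be reported as markers of failure. The documents do not support that. It requires severity to be linked both to outcome and to the taxon, and they give no strength for either link.

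**Conclusion.** The point holds as a gap in the stated analysis: confounder control is planned for the longitudinal model and not stated for the outcome comparisons or the marker search, although the same section lists the likely confounders. Taxa that track severity or comorbidity can therefore surface as outcome markers if those factors also affect outcome.

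The size is conditional. With 30% factor prevalence, 10% failure and 30 versus 270, the per-test false-positive rate is at the nominal 5% without a severity-outcome link, modestly raised at OR 2, and two to nearly four times nominal at OR 3 with shifts of 0.5 to 0.8 SD. Prevalence, odds ratio and shift are assumptions. A change is worth making because it bears directly on objectives 3 and 4 and relies on data mostly already scheduled. Whether BMI is available at Day-0 should be confirmed.

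**What to change.** Extend the planned confounder control to the outcome analyses:

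- Choose a small set of Day-0 covariates: age, sex, TB severity, comorbidity, and BMI if it is recorded at the physical examination. With about 30 failures, one clinical risk score is a sensible alternative to separate terms.
- Enter them in Adonis, and in regression-based analyses of diversity and of differential abundance. Keep the unadjusted Wilcoxon and STAMP results as descriptive.
- Report the random forest with clinical variables alone and with clinical variables plus taxa. Use the cross-validated difference to describe what the taxa add as a set. A gain in the whole model cannot qualify a single taxon, so judge individual taxa by their covariate-adjusted association with outcome.

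The cost is a few sentences of analysis text and modest extra computation. Intervals will be slightly wider and fewer taxa will qualify. The forest comparison will be noisy with about 30 failures, and should be reported with its uncertainty.

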### Ethical considerations

The study is an observational study performed in accordance with Good Clinical Practice and the Declaration of Helsinki. Ethical approval (IRB#2018-01-0656) was given by the Institutional Review Board (IRB) at the School of Public Health, Fudan University (FUSPH).. Prior to the study start, study teams of nurses, doctors and laboratory staff participated in training workshops of the study protocol and ethical considerations, led by the main study investigators from FUSPH. All participants sign an informed consent prior to enrolment in the study, or in the case of illiteracy, a fingerprint is given under observation by a witness. For each enrolled subject, a unique study identification number will be used to identify the subject’s information and sample. All the questionnaires and other study documents do not include any identifying information linked to the study code in order to maintain confidentiality for all records and data of the participants.

## Discussion

In this prospective cohort study, we present a comprehensive, multi-dimensional approach to investigate the gut microbiota in TB patients. This might be beneficial and indicative for future studies focusing on the influence of long-term using antibiotics on gut microbiota and its impact on TB treatment. The diverse microbial communities residing in our guts are found to produce bioactive compounds which can modulate host immune responses and influence the occurrence and development of distant organ diseases [3]. However, the effect of anti-TB chemotherapy on microbiome diversity is studied only recently. Reduced bacterial diversity and perturbed microbial community structures have been observed in TB patients with the comparison to healthy individuals [13, 15, 33]. Recently, a longitudinal study [34] was performed in India with an enrollment of six TB patients. The results showed that anti-TB treatment had little overall effect on the diversity of gut microbiota, but the relative abundances of specific taxa were altered after 2 months of treatment. At present, little is known about the association between gut microbiota alterations and clinical outcomes of TB patients. Large-scale and well-designed prospective cohort studies with longer follow-up are urgently needed to help us better understand the long-term use of FLDs on patients’ intestinal microbiota and the impact of gut microbiota alteration on therapeutic efficacy.

The standardized 6–8 months anti-TB treatment course with unified FLDs and prolonged use duration provides a unique opportunity to observe the effects of continuous antibiotics administration on gut microbiota. Selecting objects from different regions, with relatively large sample size and healthy controls, help to increase the representativeness of the study. Sample validity is ensured through a tightly controlled follow-up period and standardized sampling procedures. Another major strength of this study is systematically assessing the influence of administration on the human gut microbiome in a multi-center large cohort of TB patients during their entire treatment. The statistical analysis in this study will be performed from an epidemiological perspective to supplement and validate the study findings. The findings provided by this study will help us better understand the role of gut microbiota and its association with adverse effects and unfavorable treatment outcomes, which could be used to guide and personalize anti-TB treatment in the future.

In conclusion, this study will help us better understand the relationship between gut microbiota and clinical consequences of TB treatment, which will be valuable not only for Chinese TB patients but also applicable to other high TB burden countries. Based on these findings, we will be able to answer whether the gut microbiota has potential implications for the development of targeted therapeutics and better management strategies.

## Data Availability

The datasets used and/or analyzed during the current study are available from the corresponding author on reasonable request.

## Abbreviations

AFB: Acid-fast bacilli
ASVs: Amplicon sequence variants
DST: Conventional drug-susceptibility testing
EMB: Ethambutol
FLDs: First-line anti-TB drugs
FUSPH: School of Public Health, Fudan University.
GDP: Gross domestic product
GLM: Generalized linear model
INH: Isoniazid
IRB: Institutional review board
LAPs: Line-probe arrays
LJ: Lowenstein-Jensen
*M. tb*: *Mycobacterium tuberculosis*
MDR: Multidrug-resistant tuberculosis
PCR: Polymerase chain reaction
PZA: Pyrazinamide
RFP: Rifampicin
rRNA gene: ribosomal ribonucleic acid
WHO: World Health Organization
